### Randomization

Patient recruitment and the collection of written informed consent are performed at the outpatient clinic. Allocation of patients to MIDP or ODP is performed centrally by the study coordinators using a concealed online computer-controlled permuted-block randomization module (Castor EDC, CIWIT B.V., Amsterdam, the Netherlands). Randomization between MIDP and ODP will be performed in a 1:1 ratio. The block sizes will be subject to random variation with block sizes varying between 4, 6, and 8 patients. The entire randomization will be concealed to all involved investigators. Randomization will be stratified for annual distal pancreatectomy volume (< 20, 20–40, and > 40) of participating centers. In addition, randomization will be stratified for tumor involvement beyond the pancreas and spleen to correct for differences in extended resections (adrenal gland involvement is defined as extended resection according to the ISGPS guideline) [23]. Randomization will take place as soon as distal pancreatectomy is planned (i.e., date of surgery is available) in order to reduce the drop-out rate after randomization. Only patients that do not receive surgery are considered a drop-out and will not be analyzed. All other randomized patients (including patients with peroperative diagnosed metastasized disease) will be analyzed according to the intention-to-treat principle. Patients will be coded by a numeric randomization code and the study coordinator will be the only one with access to it. The source data will be stored digitally and will be kept by the project leader for 15 years after the last patient’s follow-up is completed.

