### Blinding

Within the DIPLOMA trial, all assessors of the primary outcome (i.e., the pathologists), the patients, and the adjudication committee are blinded for treatment allocation. Directly after skin closure, while still under general anesthesia, patients will receive a firmly taped, large 40 × 40 cm abdominal dressing to cover their incision(s) and therefore their treatment allocation (minimally invasive or open). This abdominal dressing will be removed when all criteria for functional recovery are met or earlier for medical reasons, such as suspicion of wound infection. If earlier inspection is required, attempts are made to maintain patient blinding. This blinding has proven to be successful in previous multicenter trials [5, 29, 30]. The success of blinding will be assessed using the blinding index as proposed by Bang et al. [31]. Both patients and pathologists will be asked about the alleged treatment allocation, based on five categories: (1) strongly believe it was MIDP, (2) somewhat believe it was MIDP, (3) somewhat believe it was ODP, (4) strongly believe it was ODP, and (5) do not know. Due to ethical and legal concerns, patient blinding will not be performed in participating centers from the USA and in patients who are intra-operatively diagnosed with irresectable disease, such as metastases. Since patient blinding only influences one of the secondary outcomes, time to functional recovery, and not the primary outcome, this is considered of minor influence. Sensitivity analysis, excluding centers from the USA and patients with perioperative diagnosed metastasized disease will be performed for analysis of time to functional recovery.

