### Secondary outcomes

The most important secondary outcomes are overall survival, time and site of disease recurrence, and postoperative time to functional recovery. Other secondary outcomes of this trial include intra-operative parameters (type of surgery (laparoscopic or robot-assisted), conversion, method of pancreatic transection, vessel resection, operative time, blood loss, and blood transfusion) and postoperative outcomes (major complications, delayed gastric emptying, pancreatic fistula, post-pancreatectomy hemorrhage, surgical site infection, serum levels of CA 19.9 and CEA, postoperative intervention, intensive care unit admission, organ failure, length of hospital stay, readmission, (time to) start of adjuvant therapy). Additional to the primary outcome, other pathology outcomes are recorded, such as tumor size, specimen length and weight, histology grading, distance from the tumor to all margins, number of retrieved lymph nodes, number of positive lymph nodes, lymphovascular and perineural tumor invasion, and venous and arterial tumor involvement. For the economical evaluation, costs (intra-operative and postoperative costs) and quality of life are assessed.

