### Statistical aspects

#### Sample size calculation

The DIPLOMA trial is designed as a non-inferiority trial, hypothesizing that in patients with pancreatic cancer the rate of microscopically radical (R0) resection rate of MIDP is non-inferior to ODP. Based on data collected for the retrospective DIPLOMA cohort study (1377 patients, matched based on propensity scores) [18], the sample size is calculated with the following assumptions: 5% one-sided significance level (*α*), 80% power (1-*β*), expected R0 rate in the open group of 58%, expected R0 resection rate in the minimally invasive group of 67%, and a non-inferiority margin of 7%. Based on these assumptions, a sample size of 226 patients (113 patients per arm) is required. Including 2.5% drop-out after randomization (patients who undergo no surgery after randomization) and 10% metastasized disease leads to a total number of patients to be randomized of 258 (129 per study arm).

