#### Statistical analysis

Primary and secondary endpoints will be crosschecked with data from primary sources, and a blinded adjudication committee will check them against the used definitions. The primary endpoint (R0 resection rate) will be tested for non-inferiority using the chi-square test as described by Dunnett and Gent [40]. The distribution of variables will be determined using several plots (boxplot, Q-Q plot, and histogram) and the Kolmogorov-Smirnov, Shapiro-Wilk, and Levene’s tests as appropriate. For comparison of normally distributed continuous variables, the independent samples *t*-test will be used and values will be expressed as means with standard deviations. Continuous non-normally distributed variables will be compared using the Mann-Whitney *U* test and values will be expressed as medians with interquartile ranges. Categorical variables will be compared by chi-square or Fisher’s exact test as appropriate, and values will be expressed as proportions. A two-tailed *p*-value < 0.05 will be considered statistically significant. Where possible, risk ratios with 95% confidence intervals will be reported. For the primary study outcome, the lower limit of the two-sided 90% confidence interval of the difference in proportions will be reported and compared with the non-inferiority margin. Time to event endpoints, such as time to functional recovery, time to recurrence, and overall survival, will be calculated using Kaplan-Meier estimations. A Cox regression analysis will be performed to investigate predictors of postoperative survival. All parameters with a *p*-value < 0.1 in a univariable analysis are included in the multivariable Cox regression analysis. Multivariable logistic regression analyses are performed to determine predictors for primary and secondary study outcomes, for example, R0 resection, the occurrence of major complications, and postoperative pancreatic fistula. Predictors for receiving adjuvant chemotherapy will be assessed and additional “as treated” analysis will be performed. Subgroup analysis will be performed comparing outcomes for patients with and without neoadjuvant chemotherapy. Intra-operative details and primary endpoint of this study are expected to be complete. For patients who are lost to follow-up, a sensitivity analysis will be performed to determine best case and worst case scenarios. A detailed statistical analysis plan will be drafted prior to database lock. Despite all prior preventive measures taken, a complex international trial may evoke unforeseen situations after database lock that threaten data integrity and can only be resolved by unlocking the database prior to the final analysis. For purpose of transparency and reproducibility, the statistical analysis plan will therefore also describe the procedure to be followed when such situations arise.

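### Kaplan-Meier for time to recurrence overstates cumulative recurrence if deaths are censored; separately, patients found metastasised at surgery stay in the set although they cannot recur

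*Protocol article*

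**What the plan says.** Under Statistical analysis, the protocol article names one estimator for three different endpoints: "Time to event endpoints, such as time to functional recovery, time to recurrence, and overall survival, will be calculated using Kaplan-Meier estimations". Under Secondary outcomes it ranks them highest: "The most important secondary outcomes are overall survival, time and site of disease recurrence, and postoperative time to functional recovery".

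The analysis set is given under Randomization. On exclusions: "Only patients that do not receive surgery are considered a drop-out and will not be analyzed". On everyone else: "All other randomized patients (including patients with peroperative diagnosed metastasized disease) will be analyzed according to the intention-to-treat principle". The sample size section allows for 10% metastasised disease and 2.5% drop-out among 258 randomised.

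Only one endpoint has an analysis without the metastasised group. Under Blinding: "Sensitivity analysis, excluding centers from the USA and patients with perioperative diagnosed metastasized disease will be performed for analysis of time to functional recovery". Nothing equivalent is stated for recurrence.

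The article does not say how a death before recurrence, or before functional recovery, is handled. It announces a detailed statistical analysis plan, to be drafted before database lock, which is not shown.

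**The concern.** Kaplan-Meier estimates the probability of an event by time t when patients leave the risk set only through the event or through censoring that carries no information. For overall survival that is reasonable. For time to recurrence, a patient who dies without recurrence can no longer recur. Censoring that patient treats the future as the same as that of those still alive, so 1-KM exceeds the proportion who actually recur.

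The setting makes this more than a formality. The earlier matched cohort, cited in the Background, had median survival of 29 and 31 months, and follow-up here is 36 months. Scheduled scans are 6 months apart for two years, then 12 months apart, so some deaths can fall between scans with no recurrence recorded.

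A second, separate problem concerns who is at risk. Patients found metastasised at surgery were never disease-free. If they enter the recurrence analysis with no possible event, they dilute the risk set.

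At stake is the stated incidence of recurrence. The Discussion calls R0 a surrogate and long-term survival the most relevant outcome for patients, so recurrence data will carry weight in any claim of oncological safety.

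**Working it through.** **1. The plan's own figure.** No figure is given for the time-to-event endpoints. The primary sample size reproduces: (1.645 + 0.842)² × (0.58×0.42 + 0.67×0.33) / (0.67 − 0.58 + 0.07)² = 112.2, so 113 per arm and 226 in all. Then 226 / (1 − 0.125) = 258.3, or 226 / (0.975×0.90) = 257.5, both in line with 258. Metastasised patients expected among those operated on: 258 × 0.975 × 0.10 = 25.2.

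**2. Recurrence, deaths censored.** Assume constant cause-specific hazards, r for recurrence and d for death without recurrence. At t = 36 months:

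- 1-KM = 1 − exp(−r·t)
- Cumulative incidence (CIF) = r/(r+d) × [1 − exp(−(r+d)·t)]

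Assumed median time to recurrence on the Kaplan-Meier scale is 18 months, so r = ln 2 / 18 = 0.0385 and 1-KM = 75.0%. The hazard d is set so that the stated share dies without recurrence by 36 months.

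| Die without recurrence (assumed) | 1-KM | CIF | Excess (points) |
|---|---|---|---|
| 2% | 75.0% | 73.9% | 1.1 |
| 5% | 75.0% | 72.3% | 2.7 |
| 10% | 75.0% | 69.5% | 5.5 |
| 20% | 75.0% | 63.8% | 11.2 |

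Check of the 10% row: d = 0.0385 × 0.100/0.695 = 0.0055. Then 1 − exp(−0.0440×36) = 0.795 = 0.695 + 0.100.

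With assumed medians of 12 to 24 months the excess runs from 0.9 to 14.6 points.

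**3. Metastasised patients kept at risk with no event.** Assume 10% of the set is metastasised, a median of 18 months to recurrence in the resected, and no deaths without recurrence among the resected. The hazard that Kaplan-Meier sees is r·N_r/(N_r + N_m), with N_r = 0.90·exp(−r·t) resected patients at risk and N_m = 0.10·exp(−m·t) metastasised patients at risk, where m is their death hazard. At 36 months, 1-KM in the whole set is 73.7% if their median survival is 6 months and 72.3% if it is 12 months, against 75.0% in the resected alone. The curve is pulled down by 1.3 to 2.7 points.

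**4. Both together.** Add an assumed 0.45% per month of death without recurrence in the resected, with metastasised median survival again 6 to 12 months. The whole-set 1-KM is then 72.1% to 73.7%. The cumulative incidence is 70.5% in the resected and 63.5% in the whole set. The Kaplan-Meier figure matches neither.

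**5. Functional recovery.** Assume a median of 5 days and read at 30 days. If 0.5%, 1%, 2% or 5% die before recovery, 1-KM exceeds the CIF by 0.5, 0.9, 1.9 or 4.7 points. The median moves from 5.00 to at most 5.12 days.

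**The case against.** The strongest reply is that the protocol does not say deaths are censored. Kaplan-Meier would be sound if death counted as an event, and for functional recovery also if patients who die were kept at risk to the end of follow-up. Event definitions, censoring rules and endpoint-specific sets are usually left to the analysis plan, which is announced. This stands in part: censoring is an inference. But the estimator itself is fixed in the protocol, for an endpoint named as time to recurrence and not as recurrence-free survival. Its ordinary meaning does not count death as an event.

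Likewise, the analysis-set rule under Randomization is a general intention-to-treat statement and does not mention recurrence. It is, however, the only set defined, and the only exception stated concerns functional recovery.

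A reader might infer more than the documents support:

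- *That recurrence and functional recovery are overstated alike.* They are not. For recovery the excess is about the share who die before recovering, and the median hardly moves. In both cases it is the cumulative probability that is too high, not the time.
- *That the metastasised patients add to the overstatement.* They act in the opposite direction, relative to the curve in resected patients.
- *That the comparison of arms is biased.* That follows only if deaths without recurrence, or the metastasised share, differ by arm, and the documents give no reason to expect it. A cause-specific hazard ratio with deaths censored remains a valid comparison of recurrence hazards.
- *That a particular size of error can be read off.* The documents give no rate of death without recurrence. At 2% the excess is about 1 point.

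**Conclusion.** The point holds for recurrence. If deaths are censored, 1-KM overstates cumulative recurrence at 36 months by about 1 to 11 points, for an assumed 2% to 20% dying without recurrence and an assumed median time to recurrence of 18 months under constant hazards. Only the 36-month follow-up comes from the protocol.

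Separately, about 25 of 258 patients who cannot recur stay in the set, which lowers the curve by about 1 to 3 points relative to resected patients under the stated assumptions. The two errors oppose each other, but nothing makes them cancel.

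The consequence lies in the absolute recurrence figures for a leading secondary outcome. The effect on functional recovery is minor. Overall survival by Kaplan-Meier is correct, and the primary R0 test is not affected. This should be corrected, but it is not a threat to the trial's main conclusion.

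**What to change.** In the statistical analysis plan, before database lock:

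- Keep Kaplan-Meier for overall survival.
- Report recurrence as Aalen-Johansen cumulative incidence with death as a competing event, with a cause-specific hazard ratio. Alternatively or additionally, report recurrence-free survival (recurrence or death) by Kaplan-Meier.
- State how patients found metastasised at surgery enter the recurrence analysis. Changing the estimator does not settle this: with no deaths among the resected, whole-set cumulative incidence would be 0.90 × 75.0% = 67.5%, the share of all operated patients who recur.
- Add a recurrence analysis in resected patients with confirmed ductal adenocarcinoma. It conditions on findings made after randomisation, so it should supplement the set defined under Randomization, not replace it, and this limitation should be stated.
- For functional recovery, keep patients who die before recovery in the risk set as never recovered, which is equivalent to cumulative incidence.

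The cost is wording in the analysis plan and standard software. No new data are needed, provided that dates of death and of recurrence are recorded, as the survival and recurrence endpoints already require.

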
### Dissemination policy

The results of this trial will be submitted to a peer-reviewed medical journal regardless of the study outcome. Authorship will be based on international guidelines. Those involved with the study who do not fulfill these criteria will be listed as “collaborator.” As soon as the trial outcomes are available, all participating patients will receive a letter with a summary of the outcomes.

## Discussion

The DIPLOMA trial is an international randomized controlled, patient- and assessor (pathologist)-blinded trial assessing the non-inferiority of MIDP compared to ODP regarding the R0 resection rate in patients with PDAC. DIPLOMA was initiated by the European Consortium on Minimally Invasive Pancreatic Surgery (E-MIPS) and is the first international trial on minimally invasive pancreatic surgery and the first to compare oncological outcomes after MIDP and ODP for PDAC.

The World Health Organization trial registry, which incorporates all international trial registries, currently (search: August 26, 2020) includes five other trials comparing MIDP (or laparoscopic distal pancreatectomy only) with ODP. One of these trials was early terminated due to lack of funding without reporting of results (NCT00988793). Two trials are currently recruiting, first, the DISPACT-2 trial, compares laparoscopic with open distal pancreatectomy regarding complications according to the comprehensive complication index. This trial has a total sample size of 294 patients with benign, premalignant, and malignant disease (DISPACT-2, DRKS00014011). The second trial compares laparoscopic with open distal pancreatectomy for pancreatic cancer. The total sample size is 306 patients and the primary outcome is recurrence-free survival (NCT03792932).

Two trials on MIDP vs ODP have been published. The multicenter Dutch LEOPARD trial compared minimally invasive with open distal pancreatectomy [5]. The second completed trial is the monocenter Swedish LAPOP trial which compared laparoscopic with open distal pancreatectomy [11]. Both trials showed shorter time to functional recovery and shorter hospital stay after the minimally invasive/laparoscopic approach [5]. Important differences between the DIPLOMA trial and the published trials are the inclusion criteria and the primary outcome. Whereas the DIPLOMA trial specifically focuses on patients with PDAC of the pancreatic body and tail, the LEOPARD and LAPOP trial included all indications for resection (i.e., also benign and premalignant lesions). The primary outcome of the LEOPARD trial was time to functional recovery and the LAPOP trial length of hospital stay whereas the DIPLOMA trial focuses on oncological outcome, with the R0 resection rate as a primary outcome and survival as the most important secondary outcome. Furthermore, time to functional recovery and quality of life will also be studied during the DIPLOMA trial. In this way, the DIPLOMA trial will assess the oncological non-inferiority of MIDP but will, as a secondary outcome, also possibly confirm the results of the LEOPARD and LAPOP trial in patients with pancreatic cancer. To decrease the influence of bias, pathologists will be blinded for the approach during specimen assessment and completion of the case report forms. In addition, patients will be blinded as was done in the LEOPARD trial [5, 41].

The most relevant outcome for patients undergoing distal pancreatectomy for PDAC would be long-term survival. However, a non-inferiority trial with survival as a primary outcome would require over 10,000 patients, which is not considered feasible. Therefore, the microscopically radical resection (R0) rate was chosen as the most relevant “surrogate” outcome. The strong association between microscopically radical resection and survival has been shown extensively [42–47]. Nevertheless, R0 rates reported in previous randomized controlled trials vary widely [48]. This is probably related to the varying pathology assessment and used definitions of R0 resection (no involvement of the margin or a distance between the margin and the tumor of at least 1 mm). Since no specific pathology assessment and reporting guidelines or protocols for distal pancreatectomy are available, the interpretation of R0 may vary between centers or even between pathologists. To minimize this heterogeneity in the DIPLOMA trial, a specific pathology assessment and reporting protocol for pancreatic body and tail specimens was developed [49]. In addition, a webinar explaining all details of this protocol including pictures and videos was developed. Participating pathologists will complete this webinar prior to inclusion of patients in their center. To reduce potential bias towards MIDP or ODP, pathologists will be blinded for treatment allocation.

Uniformity of surgical technique is an important challenge in surgical trials [50]. During several meetings, the standards for surgical technique in the DIPLOMA trial were discussed extensively and ultimately agreed upon. Several steps of the standard technique could influence the oncological outcome and subsequently the primary outcome of the trial. Whenever possible and available, existing guidelines were followed [26, 27, 49]. Since current literature regarding the benefit of performing a radical antegrade modular pancreato-splenectomy (RAMPS) procedure (for ODP) and laparoscopic radical left pancreato-splenectomy is limited, this full procedure was not included as part of the standardized technique, but it was agreed to attain to the described techniques as much as possible. However, the decision was made to include resection of Gerota’s fascia as a standard step and most importantly to adhere to the same technique for both MIDP and ODP [25, 51, 52].

## Conclusion

In conclusion, the DIPLOMA trial is an international randomized controlled, patient- and assessor (pathologist)-blinded trial, designed to assess the non-inferiority of MIDP vs. ODP for the microscopically radical (R0) resection rate of PDAC. Potentially, if the oncological non-inferiority of MIDP is confirmed, DIPLOMA will further increase the implementation of MIDP and in this way improve patient outcomes.

## Trial status

Confirmation of funding of the trial by Covidien AG (Medtronic, Neuhausen am Rheinfall, Switzerland) was received on November 15, 2017. Ethical approval in the Amsterdam UMC was received on February 01, 2018, and in University Hospital Southampton NHS Foundation Trust on February 20, 2018. The DIPLOMA trial was registered in the ISRCTN registry on April 16, 2018 (ISRCTN44897265). The current used protocol is version 3 (September 2018). The following items were included in the protocol amendments: (1) additional centers were added, further specification of blinding of the pathologist; (2) preoperative radiotherapy was removed as an exclusion criterion (before the start of the trial); and (3) three additional questionnaires (an additional quality of life questionnaire at 14 days postoperative and additional questionnaires on readmissions, complications, body image and adjuvant therapy at 3 and 12 months after surgery).

The first patient was randomized on May 03, 2018. At the time of submitting this protocol for publication (January 12, 2021), all centers were actively recruiting patients for the trial and 217 out of 258 (84%) have been randomized, which means that inclusion is on schedule.

